**Methods:**

Train your Mind was integrated into the existing school curriculum for 8 months (25 weeks excluding holidays). The effectiveness of the intervention was tested in a cluster randomized trial comprising 13 schools, 34 groups (school classes), and 800 children, using a battery of 6 computer tasks at pre- and postmeasurement. Each of the 3 core executive functions was measured by 2 tasks (Flanker and Go/No-Go; N-Back and Running Span; Attention Switching Task and Dots/Triangles). Moreover, we administered questionnaires that measure emotion-regulation, cognitive errors, physical activity, dietary habits, and the psycho-social determinants of diet and physical activity. Body mass index was also measured. Multilevel analyses will account for clustering at the school and group levels, and randomization took place at the school level.

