**Conclusions:**

The main purpose of this study is to test Train your Mind’s effectiveness in enhancing executive functions. Second, we investigate whether increased executive functions lead to improved physical activity and healthy eating. If found effective, executive function training could easily be integrated into school curricula everywhere, and as such, boost health, academic performance, and emotion-regulation of elementary school children, in a cost-effective manner.

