#### Demographics

The questionnaire package started with a short demographic background (age, school, country of birth child and parents, gender, dominant hand [as a control variable for the EF battery response button box]). Further demographic details were collected from the parents (Socioeconomic Status—a correlate of EF [42], medication).

To ensure maximal participation, both the EF test battery and the Web-based questionnaire were administered at school. Moreover, 30 identical laptops and response button boxes were used to ensure maximum accuracy in measuring reaction times. Administration of the task battery and questionnaires took place on different days, to minimize load and maximize children’s motivation to keep performing well. Everyone was measured within a span of 5 weeks, right before the start of the intervention and immediately after it ended. Trained research assistants (graduated psychology masters) were present at all times to supervise and instruct in the classrooms, as well as help slow readers work their way through the survey, when needed (this only happened a few times). All questionnaires had been normed for our age group, indicating readability should be decent. The task battery was administered in small groups of 5, the questionnaire in the entire group at once. While completing the computer task battery in small groups, children wore special noise-canceling headphones to avoid distraction. Furthermore, scores below chance levels (which indicates random responses) will be removed from the dataset. The strain on children was not small by any standards, but satisfactory pilot-testing and similar experiences in the field by supervising professors on the project team gave us confidence that the setup of measuring would run smoothly—which it did. The measurements concluded with a brief assessment of weight and height (body mass index, BMI). These anthropometrics were measured using standard procedures [43]. Both height (using the SECA 213 stadiometer) and weight (using the SECA 877 scales) were assessed without shoes or heavy clothing to the nearest 1 mm and 0.1 kg, respectively. BMI was calculated as weight/height squared (kg/m^2^) and Z-scores from age- and sex-specific reference values. Academic performance will also be taken into account during analysis using standardized national test scores (ie, CITO, the most widely used test in the Netherlands, designed by Centraal Instituur voor Toetsontwikkeling).

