### Statistical Analyses

As it was not feasible to estimate population means or SDs with our new computer task battery (designed to measure our main outcome, EF’s), and we aimed to include as many schools as was practically possible, a power analysis for this study is not included. Unfortunately, we were not able to reach the recommended critical sample size of 50 at the group level [45]. Statistical techniques to compensate for this potential lack of power for certain multilevel analyses will be considered and investigated carefully. We will assess the effectiveness of the TyM program using multilevel analyses (3 levels: student [n=800], class [n=34], and school [n=13]), to adjust for clustering of observations within a class or school. Randomization took place at the school level. The potential mediation our primary outcome, EF, exerts on our secondary outcomes (healthy behaviors: physical activity and healthy eating) will be investigated using the Baron and Kenny’s method [46], adding EFs as a covariate. Note that the intervention and measurements have been concluded, but the data have not yet been completely analyzed.

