## Discussion

This study design protocol describes the cluster randomized trial to test the effectiveness of TyM, an intervention designed to enhance EFs among elementary school children aged between 9 and 11 years. Multiple modules (focused physical activity, cognitive games, and socioemotional development) are combined in TyM to increase the chances of EFs to improve and broad transfer to occur (translation of cognitive effects into daily life improvements, such as physical activity, adaptive emotion regulation, and healthy eating). Although broad transfer has not yet been demonstrated in the field, leading experts suspect combining approaches may yield promising results [2,10-12]. TyM is novel in the sense that it combines a physical-, cognitive-, and socioemotional approach in one integrated program. The development of the intervention and why EFs are of such cardinal importance to a healthy and happy life are described in a separate paper ([name] et al, unpublished data, 2018). EFs are the very core of the entire project, which is why careful attention was paid to the measurement of these. An extensive 1 hour computer task battery was designed, with 2 tasks per sub-EF; impulse control: Flanker and Go/No-Go; working memory: N-Back and Running Span; cognitive flexibility: Attention Switching Task and Dots/Triangles. Additionally, questionnaires measured attention, concentration, emotion-regulation, social/behavioral problems, physical activity, and healthy eating. BMI was also measured. The TyM data will be enriched with academic performance and socioeconomic status from a provincial database to investigate the relations between our variables of interest. We hope to shed more light on the intricate connections between EFs, healthy behaviors, academic performance, and emotion regulation. Considering the vast array of possible positive outcomes of training EFs, efforts in this direction are warranted and justified. Given the intense nature of optimal cognitive training, and significant personal differences, combining various approaches in a playful context seemed like something teachers and pupils could continue doing wholeheartedly for a longer period of time.

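### The mediation test names EF as its one covariate, so common causes of EF and behaviour, such as socioeconomic status or baseline levels, can appear as EF mediation if EF differs between arms

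*Protocol article*

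**What the plan says.** The protocol article's Statistical Analyses section says that mediation of the healthy behaviours (physical activity and healthy eating) by EF will be tested by the Baron and Kenny method, "adding EFs as a covariate". The main effect analysis is a three-level model with 800 children, 34 classes and 13 schools. No covariate other than EF is named for the mediation step.

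The test serves a listed secondary hypothesis, that broad transfer is mediated by stronger EF. It also serves the second aim in the abstract's Conclusions: "we investigate whether increased executive functions lead to improved physical activity and healthy eating".

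The trial holds the variables that adjustment would need:
- SES comes from parents, and Demographics describes it as "a correlate of EF [42". The Discussion adds a second source: "The TyM data will be enriched with academic performance and socioeconomic status from a provincial database".
- EF was tested before and after the programme, "using a battery of 6 computer tasks at pre- and postmeasurement".
- The questionnaires on activity and diet were given at the same two waves, "right before the start of the intervention and immediately after it ended".
- Age and gender are recorded.

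**The concern.** Assigning schools supports the comparison of TyM with control. It does not support the step from EF to behaviour, because children are not assigned their EF. Suppose children from better-off families tend to have both stronger EF and healthier habits. A model containing TyM and EF but not SES then gives EF a positive coefficient even if EF does nothing to behaviour. If EF also differs between the arms, the Baron and Kenny steps can report mediation that does not exist, and part of the direct TyM effect is moved into the false indirect effect.

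Baseline EF needs a place in the model for a further reason. The Randomization section says that 3 of the 13 schools were given a condition rather than randomised, two of them because they were keen to train EF. An arm difference in post-programme EF could therefore partly predate the programme.

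At stake is the claim that EF training carries over to daily life through EF. The primary comparison of EF between arms is not affected.

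**Working it through.** The article gives no power analysis, effect size, SD, correlation or ICC, so there is no stated figure to reproduce. Only the sample sizes come from the document. Everything else is assumed and varied.

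**Model.** Variables are standardised, T is TyM and C is a common cause such as SES.
- EF = a·T + g·C + error
- Behaviour = c·T + h·C + error, with a true EF effect of zero

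**Bias.** With T and EF in the model and C left out, the EF coefficient is about g × h. The false indirect effect is a × g × h, and the direct effect falls by the same amount. At g = h = 0.3 and a = 0.3:
- EF coefficient: 0.3 × 0.3 = 0.09
- False indirect effect: 0.3 × 0.09 = 0.027
- Direct effect, if truly 0.20: 0.20 − 0.027 = 0.173

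**Is the EF coefficient significant?** Its standard error is roughly 1/√800 = 0.035. Hand calculation:

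| g = h | g × h | ÷ 0.035 | Chance of p < 0.05 |
|---|---|---|---|
| 0.1 | 0.01 | 0.28 | about 6% |
| 0.2 | 0.04 | 1.13 | about 20% |
| 0.3 | 0.09 | 2.55 | about 72% |

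Simulation with 13 schools (7 versus 6), 34 classes and 800 children agrees: 4–7% at 0.1, about 19% at 0.2, and about 73–77% at 0.3. With C in the model the rate is about 5%.

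**Is mediation declared?** A significant EF coefficient is not enough. The TyM-to-EF path must also be significant, and it is tested across only 13 schools. With 800/13 = 61.5 children per school, the design effect is 1 + 60.5 × ICC: 2.21, 4.03 and 7.05 at ICC 0.02, 0.05 and 0.10. Approximate power for a = 0.3 is then 81%, 56% and 36%. A simulation with the TyM paths tested on school means gave, at g = h = 0.3 and a = 0.3:

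| School ICC | Both paths significant | Total effect also significant (assumed 0.2 SD) |
|---|---|---|
| 0.02 | about 52% | about 22% |
| 0.05 | about 37% | about 10% |
| 0.10 | about 24% | about 4% |

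With C in both models the both-paths rate returns to about 2–4%.

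**Limits of the effect.** In an unclustered version (800 children, 2000 runs per setting), if TyM does not move EF (a = 0), false mediation stays at or below 4.4% even at g = h = 0.5. With no common cause it stays at about 5% or less. Both an arm difference in EF and a common cause of moderate strength are needed.

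**The case against.** The strongest reply is that this section is one paragraph of a condensed article. It says EF is added, not that EF is the sole covariate, and it lists no covariates for the main model either. A fuller plan may name them. The article also leans towards using these variables. The Discussion brings in SES and academic performance to study how the variables relate. Demographics promises that academic performance will be taken into account, and Randomization promises the same for the unrandomised schools.

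Part of this stands. A reader might infer that the plan excludes every other covariate. The document does not say so. Nor does it say that the EF term is the post-programme score, although a mediator of TyM must be that score or a change. None of the promised adjustments, however, names the mediation model. The Demographics and Randomization promises concern neither SES nor a baseline level. The section does commit to a method and to the term it adds, and followed as written that leaves the EF-to-behaviour path open to confounding.

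A second reply concerns size. A reader might take the 73–77% for the EF coefficient as the rate of false mediation, or think that with 800 children any small spurious association becomes significant. Neither holds. The joint rates are lower, and at correlations of 0.1 almost nothing happens.

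**Conclusion.** The concern holds in conditional form. With EF as the one named covariate, a common cause of EF and behaviour can appear as EF mediation if EF differs between arms. The documents do not support the stronger reading that it will: that depends on TyM moving EF, or on a baseline difference, and on a common cause of at least moderate strength.

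Under correlations of 0.3 and a TyM effect on EF of 0.3 SD, false mediation would be declared in roughly a quarter to a half of trials when two significant paths suffice. It would be declared in roughly 4–22% when a significant total effect is also demanded. The correlations, the effects and the ICCs are all assumptions.

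The point affects a secondary hypothesis. It is worth correcting because the article says the data are not yet completely analysed and the remedy uses data already in hand.

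**What to change.** State in Statistical Analyses that both mediation models (EF on TyM; behaviour on TyM plus post-programme EF) include the child's pre-measured score on that EF, pre-measured level of that behaviour, SES, age or grade, and gender, within the three-level structure. Say that the mediator is the post-programme score adjusted for its baseline. Present the model without these covariates as descriptive only. If a fuller plan already lists them, bring the article's statement into line with it.

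The cost is a sentence or two and a slightly longer model. Some children will lack parent-reported SES, which the provincial database can fill in part. Adjustment covers measured common causes only. It also does not settle which came first, because post-programme EF and behaviour are measured in the same wave and the 6-month follow-up was not held. The report should say so.

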## Results

Results are expected to be submitted for publication in 2018.

## Discussion

This study design protocol describes the cluster randomized trial to test the effectiveness of TyM, an intervention designed to enhance EFs among elementary school children aged between 9 and 11 years. Multiple modules (focused physical activity, cognitive games, and socioemotional development) are combined in TyM to increase the chances of EFs to improve and broad transfer to occur (translation of cognitive effects into daily life improvements, such as physical activity, adaptive emotion regulation, and healthy eating). Although broad transfer has not yet been demonstrated in the field, leading experts suspect combining approaches may yield promising results [2,10-12]. TyM is novel in the sense that it combines a physical-, cognitive-, and socioemotional approach in one integrated program. The development of the intervention and why EFs are of such cardinal importance to a healthy and happy life are described in a separate paper ([name] et al, unpublished data, 2018). EFs are the very core of the entire project, which is why careful attention was paid to the measurement of these. An extensive 1 hour computer task battery was designed, with 2 tasks per sub-EF; impulse control: Flanker and Go/No-Go; working memory: N-Back and Running Span; cognitive flexibility: Attention Switching Task and Dots/Triangles. Additionally, questionnaires measured attention, concentration, emotion-regulation, social/behavioral problems, physical activity, and healthy eating. BMI was also measured. The TyM data will be enriched with academic performance and socioeconomic status from a provincial database to investigate the relations between our variables of interest. We hope to shed more light on the intricate connections between EFs, healthy behaviors, academic performance, and emotion regulation. Considering the vast array of possible positive outcomes of training EFs, efforts in this direction are warranted and justified. Given the intense nature of optimal cognitive training, and significant personal differences, combining various approaches in a playful context seemed like something teachers and pupils could continue doing wholeheartedly for a longer period of time.

## Abbreviations

ARCES: Attention-Related Cognitive Errors Scale
AST: Attention Switching Task
BMI: body mass index
BRIEF: Behavior Rating Inventory of Executive Function
CITO: Centraal Instituur voor Toetsontwikkeling (Central Institute for the Development of Tests)
EF: executive function
FEEL-KJ: Fragebogen zur Ehrebung der Emotionsregulation bei Kindern und Jugendlichen (Questionnaire for the Assessment of Emotion Regulation among Children and Adolescents)
ISI: interstimulus interval
PAQ-C: Physical Activity Questionnaire for Children
SDQ: Strengths and Difficulties Questionnaire
SRI: stimulus and response incongruent
TyM: Train your Mind
